### Protocol history and modifications

| Date      | Protocol version | Protocol modification | Comment |
|-----------|------------------|-----------------------|---------|
| 22-Mar-05 | Version 1        | Original protocol     |         |

# **APPENDICES**

## Appendix B: Laboratory procedures for Part A

| Procedure                      | Ship to        | Assay location | Tube   | Visit:         | Tube volume (mL) |            |             |            |             |            |             |            |              |            | Total       |
|--------------------------------|----------------|----------------|--------|----------------|------------------|------------|-------------|------------|-------------|------------|-------------|------------|--------------|------------|-------------|
|                                |                |                |        |                | 1                | 2          | 3           | 4          | 5           | 6          | 7           | 8          | 9            | 10         |             |
|                                |                |                |        | Day:
Month: | Screening visit  | D0
M0   | D14
M0.5 | D28
M1  | D42
M1.5 | D84
M3  | D98
M3.5 | D168
M6 | D182
M6.5 | D273
M9 |             |
|                                |                |                |        |                | VAC1             |            |             | VAC2       |             | VAC3       |             |            |              |            |             |
| Blood Collection        |                |                |        |                |                  |            |             |            |             |            |             |            |              |            |             |
| Screening or diagnostic assays |                |                |        |                |                  |            |             |            |             |            |             |            |              |            |             |
| Screening HIV test             | Local          | Local          | SST    |                | 5                | —          | —           | —          | —           | —          | —           | —          | —            | —          | 5           |
| HIV diagnostic ELISA           | Richmond/Local | Richmond/Local | SST    |                | —                | —          | —           | —          | —           | —          | 5           | 5          | —            | 5          | 15          |
| HIV RNA PCR                    | Richmond/Local | Richmond/Local | PPT    |                | —                | 5          | —           | —          | —           | —          | 5           | 5          | —            | 5          | 20          |
| HIV DNA PCR                    | Richmond/Local | Richmond/Local | ACD    |                | —                | 10         | —           | —          | —           | —          | 10          | 10         | —            | 10         | 40          |
| HBsAg/anti-HCV/Syphilis        | Local          | Local          | SST    |                | 5                | —          | —           | —          | —           | —          | —           | —          | —            | —          | 5           |
| Safety labs                    |                |                |        |                |                  |            |             |            |             |            |             |            |              |            |             |
| CBC/ Diff/ platelets           | Local          | Local          | EDTA   |                | 5                | —          | 5           | —          | 5           | —          | 5           | —          | —            | 5          | 25          |
| Chemistry panel                | Local          | Local          | SST    |                | 5                | —          | 5           | —          | 5           | —          | 5           | —          | —            | 5          | 25          |
| T cell subsets                 | Local          | Local          | EDTA   |                | 5                | —          | 5           | —          | —           | —          | 5           | —          | —            | 5          | 20          |
| Immunogenicity assays          |                |                |        |                |                  |            |             |            |             |            |             |            |              |            |             |
| HLA typing                     | CSR            | Duke           | ACD    |                | —                | 20         | —           | —          | —           | —          | —           | —          | —            | —          | 20          |
| Humoral assay                  |                |                |        |                |                  |            |             |            |             |            |             |            |              |            |             |
| Ab to IL-12                    | CSR            | Wyeth          | SST    |                | —                | 5          | 5           | —          | 5           | —          | 5           | —          | —            | 5          | 25          |
| Cellular assays                |                |                |        |                |                  |            |             |            |             |            |             |            |              |            |             |
| ELISpot                        | CSR            | Duke           | Na Hep |                | —                | 60         | —           | —          | —           | —          | 60          | —          | —            | 60         | 180         |
| ICS                            | CSR            | FHCRC          | Na Hep |                | —                | 40         | —           | —          | —           | —          | 40          | —          | —            | 40         | 120         |
| Tetramer                       | CSR            | Wyeth          | Na Hep |                | —                | 60         | —           | —          | —           | —          | 60          | —          | —            | 60         | 180         |
| Specimen storage               |                |                |        |                |                  |            |             |            |             |            |             |            |              |            |             |
| PBMC                           | CSR            |                | Na Hep |                | —                | 80         | —           | —          | 80          | —          | 80          | 160        | —            | 160        | 560         |
| Serum                          | CSR            |                | SST    |                | —                | 10         | —           | —          | 10          | —          | 10          | 15         | —            | 15         | 60          |
| Total                   |                |                |        |                | 25        | 290 | 20   | 0   | 105  | 0   | 290  | 195 | 0     | 375 | 1300 |
| 56-Day total            |                |                |        |                | 25        | 315 | 335  | 335 | 440  | 105 | 395  | 195 | 195   | 375 |             |
| Urine Collection        |                |                |        |                |                  |            |             |            |             |            |             |            |              |            |             |
| Urinalysis                     |                |                |        |                | X                | —          | X           | —          | X           | —          | X           | —          | —            | —          |             |
| Pregnancy test                 |                |                |        |                | X                | X          | —           | X          | —           | X          | —           | X          | —            | —          |             |

Richmond = Viral and Rickettsial Disease Laboratory, California Department of Health Services (Richmond, California, USA); Duke = Duke University Medical Center (Durham, North Carolina, USA);

FHCRC/UW = Fred Hutchinson Cancer Research Center/University of Washington (Seattle, Washington, USA); CSR = Central Specimen Repository

Screening may occur over the course of several contacts/visits up to and including Day 0 prior to vaccination. Additional tests performed at screening include syphilis, HepB and HepC serologies using serum samples.

Local labs may perform HIV diagnostic algorithm (following HVTN SOP) upon approval from the HVTN Laboratory Operations Division.

For viral assays, samples are sent to Richmond; test to be performed if clinically indicated. Non-US sites may use local labs with pre-approval from the HVTN Laboratory Operations Division.

Local labs may assign other tube types for HIV diagnostics ELISA, viral assays and safety labs.

Chemistry panels are defined in Table 12-1 (pre-enrollment) and Table 12-2 (post-enrollment).

Part A immunogenicity assays will be performed retrospectively at the discretion of the Protocol Chair and the Laboratory Program Director

Based on the number of responders observed at the primary immunogenicity timepoint (in *italic* in Visit 7), humoral and cellular assays may be performed on all participants including Visit 9.

Molecular HLA typing may be performed on enrolled participants using cryopreserved PBMC collected at baseline, initially in participants who demonstrate vaccine-induced T-cell responses at post-vaccination timepoints.

## Appendix C: Laboratory procedures for Part B

| Procedure                      | Ship to        | Assay location | Tube   | Visit: | Tube volume (mL) |                 |          |             |           |             |           |             |            |              |            |              |             | Total |
|--------------------------------|----------------|----------------|--------|--------|------------------|-----------------|----------|-------------|-----------|-------------|-----------|-------------|------------|--------------|------------|--------------|-------------|-------|
|                                |                |                |        |        | Visit            |                 |          |             |           |             |           |             |            |              |            |              |             |       |
|                                |                |                |        |        | 1                | 2               | 3        | 4           | 5         | 6           | 7         | 8           | 9          | 10           | 11         | 12           | 13          |       |
|                                |                |                |        |        | Day:
Month:   | Screening visit | D0
M0 | D14
M0.5 | D28
M1 | D42
M1.5 | D84
M3 | D98
M3.5 | D168
M6 | D182
M6.5 | D273
M9 | D288
M9.5 | D364
M12 |       |
|                                |                |                |        | VAC1   |                  | VAC2            |          | VAC3        |           | VAC4        |           | VAC5        |            |              |            |              |             |       |
| Blood Collection               |                |                |        |        |                  |                 |          |             |           |             |           |             |            |              |            |              |             |       |
| Screening or diagnostic assays |                |                |        |        |                  |                 |          |             |           |             |           |             |            |              |            |              |             |       |
| Screening HIV test             | Local          | Local          | SST    | 5      | —                | —               | —        | —           | —         | —           | —         | —           | —          | —            | —          | —            | 5           |       |
| HIV diagnostic ELISA           | Richmond/Local | Richmond/Local | SST    | —      | —                | —               | —        | —           | —         | 5           | —         | 5           | —          | 5            | 5          | 5            | 25          |       |
| HIV RNA PCR                    | Richmond/Local | Richmond/Local | PPT    | —      | 5                | —               | —        | —           | —         | 5           | —         | 5           | —          | 5            | 5          | 5            | 30          |       |
| HIV DNA PCR                    | Richmond/Local | Richmond/Local | ACD    | —      | 10               | —               | —        | —           | —         | 10          | —         | 10          | —          | 10           | 10         | 10           | 60          |       |
| HBsAg/anti-HCV                 | Local          | Local          | SST    | 5      | —                | —               | —        | —           | —         | —           | —         | —           | —          | —            | —          | —            | 5           |       |
| Safety labs                    |                |                |        |        |                  |                 |          |             |           |             |           |             |            |              |            |              |             |       |
| CBC/ Diff/ platelets           | Local          | Local          | EDTA   | 5      | —                | 5               | —        | 5           | —         | 5           | —         | 5           | —          | 5            | 5          | 5            | 40          |       |
| Chemistry panel                | Local          | Local          | SST    | 5      | —                | 5               | —        | 5           | —         | 5           | —         | 5           | —          | 5            | 5          | 5            | 40          |       |
| T cell subsets                 | Local          | Local          | EDTA   | 5      | —                | 5               | —        | —           | —         | 5           | —         | —           | —          | 5            | —          | 5            | 25          |       |
| Immunogenicity assays          |                |                |        |        |                  |                 |          |             |           |             |           |             |            |              |            |              |             |       |
| HLA typing                     | CSR            | Duke           | ACD    | —      | 20               | —               | —        | —           | —         | —           | —         | —           | —          | —            | —          | —            | 20          |       |
| Humoral assay                  |                |                |        |        |                  |                 |          |             |           |             |           |             |            |              |            |              |             |       |
| HIV Binding ELISA              | CSR            | Duke           | SST    | —      | 5                | —               | —        | —           | —         | —           | —         | 5           | —          | 5            | —          | 5            | 20          |       |
| Ab to GM-CSF                   | CSR            | Wyeth          | SST    | —      | 5                | —               | —        | —           | —         | —           | —         | 5           | —          | 5            | —          | 5            | 20          |       |
| Ab to IL-12                    | CSR            | Wyeth          | SST    | —      | 5                | 5               | —        | 5           | —         | 5           | —         | —           | —          | —            | —          | 5            | 25          |       |
| Cellular assays                |                |                |        |        |                  |                 |          |             |           |             |           |             |            |              |            |              |             |       |
| ELISpot                        | CSR            | Duke           | Na Hep | —      | 60               | —               | —        | —           | —         | 60          | —         | —           | —          | 60           | —          | 60           | 240         |       |
| ICS                            | CSR            | FHCRC          | Na Hep | —      | 40               | —               | —        | —           | —         | 40          | —         | —           | —          | 40           | —          | 40           | 160         |       |
| Tetramer                       | CSR            | Wyeth          | Na Hep | —      | 60               | —               | —        | —           | —         | 60          | —         | 60          | —          | 60           | —          | 60           | 300         |       |
| Tcell repertoire studies       | CSR            | Vanderbilt     | Na Hep | —      | —                | —               | —        | —           | —         | 50          | —         | 50          | —          | 50           | 50         | 50           | 250         |       |
| Specimen storage               |                |                |        |        |                  |                 |          |             |           |             |           |             |            |              |            |              |             |       |
| PBMC                           | CSR            |                | Na Hep | —      | 80               | —               | —        | 80          | —         | 90          | 90        | 160         | 100        | 100          | 160        | 160          | 1020        |       |
| Serum                          | CSR            |                | SST    | —      | 10               | —               | —        | 10          | —         | 10          | 15        | 15          | 15         | 15           | 15         | 15           | 120         |       |
| Total                          |                |                |        | 25     | 300              | 20              | 0        | 105         | 0         | 350         | 105       | 325         | 115        | 370          | 255        | 435          | 2405        |       |
| 56-Day total                   |                |                |        | 25     | 325              | 345             | 345      | 450         | 105       | 455         | 105       | 430         | 115        | 485          | 255        | 435          |             |       |
| Urine Collection               |                |                |        |        |                  |                 |          |             |           |             |           |             |            |              |            |              |             |       |
| Urinalysis                     |                |                |        | X      | —                | X               | —        | X           | —         | X           | —         | X           | —          | X            | —          | —            |             |       |
| Pregnancy test                 |                |                |        | X      | X                | —               | X        | —           | X         | —           | X         | —           | X          | —            | X          | —            |             |       |

Richmond = Viral and Rickettsial Disease Laboratory, California Department of Health Services (Richmond, California, USA); Duke = Duke University Medical Center (Durham, North Carolina, USA);

FHCRC/UW = Fred Hutchinson Cancer Research Center/University of Washington (Seattle, Washington, USA); CSR = Central Specimen Repository

Screening may occur over the course of several contacts/visits up to and including Day 0 prior to vaccination. Additional tests performed at screening include syphilis, HepB and HepC serologies using serum samples.

Local labs may perform HIV diagnostic algorithm (following HVTN SOP) upon approval from the HVTN Laboratory Operations Division.

For viral assays, samples are sent to Richmond; test to be performed if clinically indicated. Non-US sites may use local labs with pre-approval from the HVTN Laboratory Operations Division.

Local labs may assign appropriate alternative tube types for locally performed tests.

Chemistry panels are defined in Table 12-1 (pre-enrollment) and Table 12-2 (post-enrollment).

Molecular HLA typing may be performed on enrolled participants using cryopreserved PBMC collected at baseline, initially in participants who demonstrate vaccine-induced T-cell responses at post-vaccination timepoints.

Based on the number of responders observed at the primary immunogenicity timepoint (in *italic* in Visit 11), humoral and cellular assays may be performed on all participants, including Visits 7 and 13.

## Appendix D: Procedures at HVTU

| Procedure                                                    |         | Visit           |      |      |      |      |      |      |      |      |      |      |      |      |      |
|--------------------------------------------------------------|---------|-----------------|------|------|------|------|------|------|------|------|------|------|------|------|------|
|                                                              | Visit:  | 01 a | 02   | 03   | 04   | 05   | 06   | 07   | 08   | 09   | 10   | 11   | 12   | 13   | Post |
|                                                              | Day:    | Screening       | D0   | D14  | D28  | D42  | D84  | D70  | D168 | D182 | D273 | D287 | D364 | D455 |      |
|                                                              | Month:  |                 | M0   | M.5  | M1   | M1.5 | M3   | M3.5 | M6   | M6.5 | M9   | M9.5 | M12  | M15  |      |
|                                                              | Part A: |                 | VAC1 |      | VAC2 |      | VAC3 |      |      |      |      |      |      |      |      |
| Part B:                                                      |         | VAC1            |      | VAC2 |      | VAC3 |      | VAC4 |      | VAC5 |      |      |      |      |      |
| Study procedures                                             |         |                 |      |      |      |      |      |      |      |      |      |      |      |      |      |
| Signed screening consent (if used)                           |         | X               | –    | –    | –    | –    | –    | –    | –    | –    | –    | –    | –    | –    | –    |
| Assessment of understanding                                  |         | X               | –    | –    | –    | –    | –    | –    | –    | –    | –    | –    | –    | –    | –    |
| Signed protocol consent                                      |         | X               | –    | –    | –    | –    | –    | –    | –    | –    | –    | –    | –    | –    | –    |
| Medical history                                              |         | X               | –    | –    | –    | –    | –    | –    | –    | –    | –    | –    | –    | –    | –    |
| Complete physical exam                                       |         | X               | –    | –    | –    | –    | –    | –    | –    | –    | A    | –    | –    | B    | –    |
| Obtain demographics                                          |         | X               | –    | –    | –    | –    | –    | –    | –    | –    | –    | –    | –    | –    | –    |
| Confirm eligibility                                          |         | X               | –    | –    | –    | –    | –    | –    | –    | –    | –    | –    | –    | –    | –    |
| Randomize participant                                        |         | X               | –    | –    | –    | –    | –    | –    | –    | –    | –    | –    | –    | –    | –    |
| Abbreviated physical exam                                    |         | –               | X    | X    | X    | X    | X    | X    | X    | B    | B    | B    | B    | –    | –    |
| Risk reduction/pregnancy prevention counseling               |         | X               | X    | X    | X    | X    | X    | X    | X    | B    | X    | B    | B    | B    | –    |
| Behavioral risk assessment                                   |         | X               | –    | –    | –    | –    | –    | –    | –    | –    | –    | –    | –    | –    | –    |
| Social impact assessment                                     |         | –               | –    | –    | –    | –    | X    | –    | X    | –    | A    | –    | –    | B    | –    |
| Outside testing and belief questionnaire                     |         | –               | –    | –    | –    | –    | X    | –    | –    | –    | A    | –    | –    | B    | –    |
| Concomitant medications                                      |         | X               | X    | X    | X    | X    | X    | X    | X    | B    | X    | B    | B    | B    | –    |
| Intercurrent illness / adverse experience                    |         |                 | X    | X    | X    | X    | X    | X    | X    | B    | X    | B    | B    | B    | –    |
| HIV infection assessment/results b                |         | X               | –    | –    | –    | –    | –    | X    | A    | B    | A    | B    | B    | B    | –    |
| Local lab assessment                                         |         |                 |      |      |      |      |      |      |      |      |      |      |      |      |      |
| Pregnancy (urine or serum HCG) c                  |         | X               | X    | –    | X    | –    | X    | –    | X    | –    | B    | –    | B    | –    | –    |
| Urine dipstick                                               |         | X               | –    | X    | –    | X    | –    | X    | –    | B    | –    | B    | –    | –    | –    |
| CBC, differential, platelet d                     |         | X               | –    | X    | –    | X    | –    | X    | –    | B    | A    | B    | B    | B    | –    |
| Chemistry panel (see Table 12-1 and Table 12-2) d |         | X               | –    | X    | –    | X    | –    | X    | –    | B    | A    | B    | B    | B    | –    |
| RPR, Hepatitis B, Hepatitis C                                |         | X               | –    | –    | –    | –    | –    | –    | –    | –    | –    | –    | –    | –    | –    |
| T cell subsets                                               |         | X               | –    | X    | –    | –    | –    | X    | –    | –    | A    | B    | –    | B    | –    |
| Vaccination procedures                                       |         |                 |      |      |      |      |      |      |      |      |      |      |      |      |      |
| Vaccination                                                  |         | –               | X    | –    | X    | –    | X    | –    | B    | –    | B    | –    | –    | –    | –    |
| Reactogenicity assessments e                      |         | –               | X    | –    | X    | –    | X    | –    | B    | –    | B    | –    | –    | –    | –    |
| Post-study                                                   |         |                 |      |      |      |      |      |      |      |      |      |      |      |      |      |
| Unblind participant                                          |         | –               | –    | –    | –    | –    | –    | –    | –    | –    | –    | –    | –    | –    | X    |

“X” denotes procedure is to be performed in both parts of study. “A” denotes procedure is to be performed in Part A only. “B” denotes procedure is to be performed in Part B only.

a Screening may occur over the course of several contacts/visits up to and including Day 0 prior to vaccination.

b Includes pre- and post-test counseling and follow-up contact to report results to participant.

c For female participants, pregnancy test must be performed on the day of vaccination prior to vaccination. Pregnancy test to determine eligibility may be performed at screening or on Day 0 prior to first vaccination. Serum pregnancy tests may be used to confirm the results of, or substitute for, a urine pregnancy test.

d Blood draws required at post-enrollment vaccination visits must be performed prior to administration of study agent; however, it is not necessary to have results prior to administration. Lab tests may be drawn within the 3 days prior to vaccination.

e Reactogenicity assessments performed daily for up to 3 days post-vaccination (see Section 14.1).

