## 7 Study type, study population, and eligibility criteria

The study is a Phase I multicenter, randomized, placebo-controlled, double-blind trial to evaluate the safety and immunogenicity of HIV-1 *gag* DNA vaccine alone and in combination with *IL-12* DNA adjuvant as a 3 dose priming series. Due to differences in injection volumes, study participants and study staff cannot be blinded to study group assignment. The study is double-blinded regarding vaccine study product versus placebo administration. Participants in Part B will also receive 2 booster vaccinations either with the above plasmids or with HIV CTL MEP vaccine or with placebo. Participants will be recruited and screened. Those determined to be eligible, based on the inclusion and exclusion criteria (see Table 7-1 and Table 7-2), will be enrolled in the study and followed for a total period of 9 months in Part A and 15 months in Part B.

Participants will receive priming series vaccinations at Days 0, 28, and 84 (Months 0, 1 and 3). Booster vaccinations for participants in Part B will be administered at Days 168 and 273 (Months 6 and 9). All vaccinations will be administered by intramuscular injection in the deltoid using needle/syringe in the outpatient setting.

Participants will be healthy HIV-1-uninfected (seronegative) adults who comprehend the purpose of the study and have provided written informed consent.

See Table 7-1 for inclusion criteria and Table 7-2 for exclusion criteria. Final eligibility determination will depend on results of laboratory tests, medical history, physical examinations, and answers to the self-administered and/or interview questions.

See Table 12-1 for screening procedures.

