### **8.7.2 Cellular immunogenicity studies for Part A (HVTN)**

#### **8.7.2.1 IFN- $\gamma$ ELISpot**

Bulk T cell responses will be assessed by IFN- $\gamma$  ELISpot using cryopreserved peripheral blood mononuclear cells (PBMC) stimulated overnight with synthetic peptide pools that span the proteins encoded by the vaccine constructs. ELISpot assays will be performed at baseline and 2 weeks post final (third) vaccination. Additional time points may be assayed if positive responses are observed at the primary immunogenicity time point (see Appendix B). Responses will be reported as number of spot forming cells per  $10^6$  cells/well recognizing any specific peptide pool.

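### Appendix D dates Visit 7 at Day 70, 14 days before the third vaccination it is meant to follow, while Appendices B and C give Day 98; the visit schedules must be reconciled

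*Protocol*

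**What the plan says.** Section 7 fixes the priming schedule: "Participants will receive priming series vaccinations at Days 0, 28, and 84 (Months 0, 1 and 3"). The third vaccination is therefore Day 84, Visit 6.

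Three appendices then date the visits, and Section 12 tells sites to carry out procedures at the time points in all three.

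- **Appendix D** (site procedures), Day row from Visit 6: "D84 | D70 | D168 | D182 | D273 | D287 | D364 | D455". The Month row beneath it, from the same visit, runs "M3 | M3.5 | M6 | M6.5". Visit 7 is thus Day 70 and Month 3.5 in one column.
- **Appendix B** (Part A laboratory): "D84 M3 | D98 M3.5 | D168 M6 | D182 M6.5 | D273 M9". Visit 7 is Day 98.
- **Appendix C** (Part B laboratory): Visit 7 is also Day 98, Month 3.5. For the last booster and the two visits after it, the row reads "D273 M9 | D288 M9.5 | D364 M12", so Visit 11 is Day 288. Appendix D has Day 287.

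Section 8.7.2.1 sets the Part A cellular sampling: "ELISpot assays will be performed at baseline and 2 weeks post final (third) vaccination". Section 8.7.2.2 sets the same time for intracellular cytokine staining. Sections 8.7.4.2 and 8.7.4.3 use that point in Part B for anti-IL-12 antibody and tetramer samples.

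A footnote to Appendix B says that, depending on the number of responders at Visit 7, "humoral and cellular assays may be performed on all participants including Visit 9". In Appendix B every Part A blood row at Visit 9 is a dash and the column total is 0 mL. In Appendix D every Visit 9 entry is either Part B only or blank.

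**The concern.** Appendix D is the schedule that clinic staff work from, and one of its days cannot be right as printed: Visit 7 would precede Visit 6. Visit 7 carries the first safety laboratory tests after dose 3 in both parts (blood count, chemistry, T-cell subsets, urine dipstick). Safety is the primary objective, and Sections 4.1 and 4.2 state that neither the gag plasmid nor the IL-12 plasmids have been tested in humans. Post-vaccination laboratory abnormalities also feed the pause rules in Tables 14-2 and 14-3. Samples taken on Day 70 would describe the participant after two doses but be filed as post-dose-3 data.

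The Visit 9 footnote and the Visit 11 day are smaller faults in the same set of tables.

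**Working it through.** **1. Day offsets.**

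- Visit 7 by Appendix D: 70 − 84 = −14 days from dose 3.
- Visit 7 by Appendices B and C: 98 − 84 = +14 days, which is the two weeks of Section 8.7.2.
- Gap between the two dates: 98 − 70 = 28 days.
- Visit 11, with the fifth vaccination on Day 273: 287 − 273 = 14 days (Appendix D); 288 − 273 = 15 days (Appendix C).

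**2. Which day do the printed blood totals use?** Appendices B and C give a running 56-day total at each visit.

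Inputs are the column totals. Part A: 25, 290, 20, 0, 105, 0, 290, 195, 0, 375 mL, which re-add from the assay rows and sum to the printed 1300 mL. Part B: 25, 300, 20, 0, 105, 0, 350, 105, 325, 115, 370, 255, 435 mL, as printed. Screening is taken as the day before Day 0.

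Rule: the total at a visit is the sum of all draws dated on that day or up to and including 56 days before it.

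With Visit 7 at Day 98 the window opens on Day 42:

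- Part A: 105 + 0 + 290 = 395 mL; printed 395.
- Part B: 105 + 0 + 350 = 455 mL; printed 455.

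All 10 Part A totals and all 13 Part B totals reproduce exactly.

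With Visit 7 at Day 70 its window opens on Day 14, and the Day 84 window (from Day 28) also takes in the Visit 7 draw:

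| Running total, mL | Printed | With Day 98 | With Day 70 |
|---|---|---|---|
| Part A, Visit 6 | 105 | 105 | 0 + 105 + 290 + 0 = 395 |
| Part A, Visit 7 | 395 | 395 | 20 + 0 + 105 + 290 = 415 |
| Part B, Visit 6 | 105 | 105 | 0 + 105 + 350 + 0 = 455 |
| Part B, Visit 7 | 455 | 455 | 20 + 0 + 105 + 350 = 475 |

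If the window excludes the 56th day, neither date reproduces the whole row: Day 98 then gives 290 and 350 mL at Visit 7, and Day 70 still gives 395 and 455 mL at Visit 6 against a printed 105. Only Day 98 with an inclusive window fits everywhere.

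**3. What is left after dose 3 if Visit 7 is held on Day 70?**

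- Part A: blood count and chemistry are scheduled at screening and Visits 3, 5, 7 and 10. The next after Day 84 is Visit 10, Day 273: 273 − 84 = 189 days.
- Part B: they are scheduled at screening and Visits 3, 5, 7, 9, 11, 12 and 13. The next after Day 84 is Visit 9, Day 182, which is 98 days after dose 3 and 14 days after dose 4 (Day 168). None falls between doses 3 and 4.

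**4. Part A specimens after Visit 7 (Appendix B).**

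- Visit 8: HIV diagnostics, with 160 mL for stored PBMC and 15 mL for serum; total 195 mL.
- Visit 9: 0 mL.
- Visit 10: ELISpot 60 mL, cytokine staining 40 mL, tetramer 60 mL, anti-IL-12 5 mL, stored PBMC 160 mL and serum 15 mL, plus diagnostics and safety tests; total 375 mL.

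**The case against.** The strongest reply is that Day 70 corrects itself. The visit number, the Month 3.5 label, two other appendices and Section 8.7.2 all disagree with it, and a coordinator would have to hold Visit 7 before Visit 6 to obey it. Visit windows are in the Study Specific Procedures, which are not shown and may state the day correctly. This stands, and it makes actual mistiming unlikely.

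It can also be said that no planned safety decision waits on Visit 7. Dose escalation (Section 8.3) and the move to Part B (Section 8.4) use data to two weeks after the second vaccination, and reactogenicity is collected for three days after every dose. That is right for those two reviews. It is not right for the pause rules, which act on laboratory abnormalities whenever they are found.

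Three stronger readings are tempting, and the document supports none of them.

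- *That 156 participants would have 290 to 350 mL drawn on the wrong day.* That is a ceiling requiring every site to follow the one impossible entry. The volumes and immunogenicity draws are specified only in Appendices B and C, which say Day 98. Appendix D lists for Visit 7 the examination, counselling, medication and adverse-event review, HIV assessment and safety laboratory tests.
- *That the later Part A immune assays could not be run because Visit 9 has no blood.* Visits 8 and 10 supply stored specimens, and Visit 10 has dedicated assay draws. The footnote is permissive, and Section 8.7.2 allows additional time points by general reference to Appendix B. Part A assays are in any case discretionary and, by Section 5.1, depend on responses in Part B.
- *That Day 70 would breach the blood limit.* The recalculated Visit 6 and 7 totals peak at 475 mL, under the 500 mL per 8 weeks in Section 12.3.

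**Conclusion.** The contradiction holds. Appendix D places Visit 7 14 days before dose 3, against its own month label, Appendices B and C, Section 8.7.2 and the printed 56-day totals. Because Section 12 makes all three appendices operative, the conflict is in a working instruction.

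If the printed day were followed, the cost would be the early laboratory check after dose 3: a 189-day gap in Part A, and in Part B no scheduled blood count or chemistry between doses 3 and 4. The chance of this at many sites is low because the surrounding entries expose the error.

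The Visit 11 difference is one day. The Visit 9 footnote is a wrong reference that removes no specimen and no assay. No sample size, endpoint definition or analysis method is affected.

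This assumes that the Day row was extracted faithfully (the neighbouring entries are intact) and that the Appendix C days are read in order, since its header is displaced by a column in the extracted text. The protocol history lists only Version 1, so no correction is on record there.

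**What to change.** Issue a clarification memo before enrollment, a route that the Protocol history section provides for. It should:

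1. Reconcile the Appendix D Day row for Visits 7 and 11 with Appendices B and C and with Section 8.7, so that each visit has a single day throughout.
2. Amend the Appendix B footnote to name a Part A visit at which specimens are collected.
3. Confirm that the Study Specific Procedures carry the reconciled days.

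Which day applies is for the sponsor to settle. The cost is a short memo and a check of site scheduling tools; sample size, assays and analysis are unchanged.
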